### Provisions for post-trial care

Any patients who suffer harm from trial participation will be covered by the Japanese public healthcare system.

### Clinical assessments

On enrollment in this trial, clinical research physicians will obtain information from the patients including age, sex, past history, current medication, causative disease of pain (central post-stroke pain, post–spinal cord injury pain, failed back surgery syndrome, complex regional pain syndrome, post-herpetic neuralgia, diabetic neuropathic pain, peripheral arterial disease, or others), lesion site causing pain (central or peripheral), location of pain (arm, leg, lower back, back, chest, face), laterality of pain (left, right, midline), degree of paralysis (none, mild, moderate, severe), sensory disturbance (hypoesthesia, allodynia, numbness), and duration of disease. During the SCS trial, the degree of pain will be evaluated using a VAS according to the plan (Fig. 1). After SCS system implantation, assessment items will be evaluated according to the plan, including the degree of improvement with respect to pain relief and mental state (Table 2).

**Table 2 Tab2:**
[figure not shown]
Summary of observations, assessment items, and schedule of assessments

*VAS* visual analog scale, *SF-MPQ-2* Short-Form McGill Pain Questionnaire-2, *PCS* Pain Catastrophizing Scale, *QIDS-J* Quick Inventory of Depressive Symptomatology, *MRI* magnetic resonance image, *Xp* X-ray picture, *CT* computed tomography, *SCS* spinal cord stimulation

### Assessment items

Assessments of pain relief will be performed using the VAS and Short-Form McGill Pain Questionnaire-2 (SF-MPQ-2), and mental state will be assessed using the Pain Catastrophizing Scale (PCS) and Quick Inventory of Depressive Symptomatology (QIDS-J).

### Imaging evaluation

Before the SCS trial, whole-spine magnetic resonance imaging and X-ray examinations will be performed to rule out any abnormal findings. After the SCS trial and SCS system implantation, spinal X-ray and computed tomography examinations will be performed to confirm the location of the SCS leads and to rule out postoperative complications.

### Primary outcome

The primary analysis will compare the pain improvement between the new stimulation patterns (DTM or FAST) and the conventional tonic stimulation in the SCS trial. The pain improvement of each stimulation pattern in the SCS trial is defined as effective when the VAS value decreases by 33% or more compared to the VAS value before the start of each stimulation pattern. The primary outcome will be analyzed at the end of the SCS trial.

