**Discussion:**

This study aims to clarify the effectiveness of the latest new stimulation patterns compared to the conventional tonic stimulation. In addition, which stimulation pattern is most effective for which kind of causative disease will be clarified.

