### Secondary outcomes

The following secondary outcomes will be analyzed at the end of the SCS trial: (1) the relationship between causative disease and improvement rates by each stimulation pattern and (2) comparison of the improvement rates between DTM and FAST stimulation patterns in all cases and by causative disease.

After SCS system implantation, the efficacy of SCS is defined as when the VAS value decreases by 33% or more compared to the VAS value before the implantation. Long-term effect is defined as continuing the efficacy of SCS for more than 12 months. The following secondary outcomes will be assessed for six times during 24 months’ follow-up periods after the implantation (Table 2): (3) changes in assessment items including the VAS, SF-MPQ-2, PCS, and QIDS-J preoperatively, and at 1, 3, 6, 12, 18, and 24 months after the implantation; (4) preoperative factors associated with the long-term effects; and (5) adverse events related to this study 3 months after the SCS system implantation. Data will be presented as mean and standard deviation for continuous variables (including VAS score, SF-MPQ-2 score, PCS score, and QIDS-J score).

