### Sample size

The study’s sample size is based on the expected difference of the percentage of patients achieving pain improvement between the new and conventional tonic stimulation patterns.

We assumed that the percentages of pain improvement will be 80% for the new stimulation patterns (DTM or FAST) [15, 17] and 50% for the conventional tonic stimulation pattern [25–28] by reviewing the literature. The required sample size was calculated to be 78 cases with a significance level of 0.05, a power of 80%, and 1:1 allocation. Each group (A, B, C, and D) will enroll 20 cases (40 conventional tonic stimulation and 40 new stimulation patterns in Stim-1). Thus, it is possible to secure a power of 0.8 even with the analysis of Stim-1 alone. In addition, considering the insufficient sample size caused by patient detachment during the research process, it is necessary to expand the target number of cases is 23 in each group, resulting in a total sample size of 92 patients in all groups. Assuming, based on past performance, that there are 2–4 cases enrolled in the SCS trial per month, 24–48 patients are expected to be enrolled annually. Therefore, the target number is expected to be reached in 2 to 4 years.

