The secondary outcome will be analyzed as follows:Similar analyses of the primary outcome analysis will be performed for each causative disease.Comparison of DTM and FAST stimulation patterns for pain improvement in Stim-3. Pain improvements will be compared between DTM and FAST stimulations using logistic regression analysis adjusted for the treatment group (DTM stimulation, FAST stimulation) and pre-VAS value. Similar analyses will be performed by causative disease.Adjusted mean values and 95% confidence intervals of changes in assessment items including the VAS, SF-MPQ-2, PCS, and QIDS-J before the SCS system implantation, and at 1, 3, 6, 12, 18, and 24 months after SCS system implantation at each time point will be calculated using a linear mixed model with the interaction between treatment group and time point as a fixed effect. Analysis will be performed using a linear mixed model with the change rate and change amount of each indicator as outcome variables. The rate and amount of changes in each index at each evaluation time point will be compared between groups using fixed effects such as pretreatment value of each index, treatment group, evaluation time point, and interaction between the treatment group and evaluation time point. The 12-month analysis will be performed at preoperative, 1, 3, 6, and 12 months, and the 24-month analysis will be performed at 18 months and the final follow-up (24 months).In participants with no missing VAS values preoperatively to 12 months after implantation, analyses of the prognostic factors related to the long-term effect of continuing 33% reduction in the pain VAS over 12 months will be performed using logistic analysis with the following explanatory variables: treatment group, pre-implantation VAS value, sex, age, causative disease, site of pain, degree of paralysis, degree of sensory disturbance, and disease duration.

A comparison between the new and conventional stimulation patterns will be performed with Stim-1and Stim-2. A comparison between DTM and FAST, which is the new stimulation pattern, will be performed with Stim-3. Therefore, this study is designed to compare the VAS improvement rates in different stimulation patterns, so it is not necessary to consider multiplicity.

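### DTM and FAST are compared with tonic only as one pooled group, so no DTM-tonic or FAST-tonic estimate is planned, although secondary outcome 1 is defined by each pattern

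*Protocol article*

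**What the plan says.** Protocol article, Primary outcome: the comparison is between "the new stimulation patterns (DTM or FAST) and the conventional tonic stimulation in the SCS trial". Under Statistical analysis, the opening sentence speaks of comparing each stimulation, but the treatment variable then listed has two levels, new and tonic. Data come from Stim-1 and Stim-2, or from Stim-1 alone if the carryover test is positive.

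Secondary outcomes: outcome 1 is "the relationship between causative disease and improvement rates by each stimulation pattern". The analysis given for it under Statistical analysis is "Similar analyses of the primary outcome analysis will be performed for each causative disease".

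DTM and FAST are separated in one place only. This is secondary outcome 2, a logistic regression in Stim-3 that is repeated by causative disease. In Table 1, Stim-3 is FAST for Groups 1 and 2 and DTM for Groups 3 and 4, so tonic is absent.

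The Discussion paragraph of the Abstract states the aim that "which stimulation pattern is most effective for which kind of causative disease will be clarified". The Background and the main Discussion repeat this as the second clinical question.

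Statistical analysis also states that multiplicity need not be considered. Its reason is that new-versus-tonic uses Stim-1 and Stim-2 while DTM-versus-FAST uses Stim-3.

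**The concern.** The second clinical question concerns three patterns. Ranking them, overall or within a disease, needs DTM against tonic and FAST against tonic. The outcome definition promises results for each pattern, but the model attached to it merges two of the three. Run as written, it does not deliver the quantity that the outcome names.

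The same gap affects how the primary result is read. The hypothesis speaks of the latest patterns in the plural, and the sample size gives both the same 80% responder rate. If only one pattern works, the pooled test can still succeed, and the report would contain no estimate showing whether the other beats tonic. The Background says that only one of the new patterns can be used after implantation, so readers will want the answer for each.

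**Working it through.** **Inputs.** The Sample size section assumes "the percentages of pain improvement will be 80% for the new stimulation patterns (DTM or FAST") and "50% for the conventional tonic stimulation pattern". It also states: "Each group (A, B, C, and D) will enroll 20 cases (40 conventional tonic stimulation and 40 new stimulation patterns in Stim-1"). By Table 1, the 40 new patients in Stim-1 are 20 on DTM (Group 2) and 20 on FAST (Group 4). The article gives no within-patient correlation of response. A latent correlation of 0 to 0.7 is assumed here, with no period or carryover effect.

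**Reproducing the plan's figure.** "The required sample size was calculated to be 78 cases with a significance level of 0.05, a power of 80%, and 1:1 allocation". With two-sided alpha, pooled variance and no continuity correction:

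n per arm = [1.96·√(2·0.65·0.35) + 0.8416·√(0.8·0.2 + 0.5·0.5)]² / 0.30² = (1.322 + 0.539)² / 0.09 = 38.5, so 39 per arm and 78 in total. This matches.

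Power = Φ[(|p1 − p2| − 1.96·SE0) / SE1], where SE0 uses the pooled rate and SE1 the separate rates. At 40 versus 40 this gives 81.6%, in line with the article's claim for Stim-1 alone.

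**One new pattern at 80%, the other equal to tonic at 50%.**

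- *Stim-1 fallback.* The pooled new rate is (20·0.80 + 20·0.50)/40 = 65%, against 50%. SE0 = 0.1105 and SE1 = 0.1093, so power = Φ[(0.15 − 0.2166)/0.1093] = 27%.
- *Crossover on Stim-1 and Stim-2*, simulated with a paired test as a stand-in for the planned logistic model, 20 per group:

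| Latent correlation | Pooled test favours new | 80% pattern alone beats tonic | 50% pattern alone beats tonic |
|---|---|---|---|
| 0 | 47% | 82% | 2% |
| 0.3 | 56% | 88% | 2% |
| 0.5 | 64% | 92% | 2% |
| 0.7 | 73% | 97% | 2% |

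A linear probability model with cluster-robust standard errors gives 50%, 58% and 75% for the pooled test at correlations 0, 0.4 and 0.7. The range is therefore about 47% to 75%. With 23 per group the paired test gives 54% to 79%.

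- *Planned Stim-3 comparison*, 40 versus 40 at 80% against 50%: about 82%. Simulated jointly with the pooled test, a pooled win with no Stim-3 signal occurs in about 9% to 13% of trials.

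**Weaker pattern at 65% instead of 50%.** In Stim-3, SE0 = 0.0998 and SE1 = 0.0984, so power = Φ[(0.15 − 0.1957)/0.0984] = about 32%. The pooled test wins in about 85% to 98%.

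**Can the design supply the missing contrasts?** Yes. Groups 1 and 2 receive tonic and DTM in Stim-1 and Stim-2, and Groups 3 and 4 receive tonic and FAST. Each contrast therefore has 40 within-patient pairs. At 80% versus 50% and alpha 0.05, power per pattern is about 82% to 97%. In the Stim-1 fallback (20 of one pattern versus 40 tonic), the pooled rate is 36/60 = 0.60, SE0 = 0.1342 and SE1 = 0.1194, so power = Φ[(0.30 − 0.2630)/0.1194] = 62%.

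**The case against.** Pooling is the declared question. The hypothesis, primary outcome, sample size and model all treat the new patterns as a class, and any class-level test can be positive when only one member works. This stands: the pooled primary test is not an error.

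The plan also has its own check. Stim-3 is a randomised DTM-FAST comparison, and in the 80%/50% scenario it would usually show that the patterns differ. This stands in part. The 47% to 75% figure should not be quoted without it. But Stim-3 contains no tonic, so it cannot say whether the weaker pattern beats tonic, and at 80% against 65% it usually misses the difference.

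Three stronger readings are tempting and are not supported:

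- A reader might infer that secondary outcome 1 is never estimated at all. Tonic has its own level in the by-disease model, and DTM versus FAST is planned by disease. Only the two contrasts with tonic are absent.
- A reader might infer that a pooled win would steer patients to the wrong device. Study procedures chooses the device from the pattern that was effective in that patient's own SCS trial.
- A reader might expect nearly 100% power per pattern from a three-level model on all three periods. That borrows Stim-3 data, which inform a tonic contrast only under additive period effects and no carryover.

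Finally, the article condenses a fuller protocol, and an unseen analysis plan might add by-pattern rates. That would be welcome, but the article does state a model for this outcome, and that model does not match the definition.

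**Conclusion.** The point holds as a mismatch between an outcome and its analysis, and as a limit on what the primary result can show. No stated model gives DTM against tonic or FAST against tonic, overall or by disease, so the three-pattern question is only partly answerable. A positive pooled test supports the class, not each member.

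If one pattern equals tonic, the pooled crossover test still succeeds in about half to three quarters of trials (about 27% in the Stim-1 fallback). In most of these wins the planned Stim-3 comparison would show a difference between the new patterns. These figures rest on the assumed correlation range, no period or carryover effect, 20 patients per group, and simple tests standing in for the logistic model. The textual mismatch does not depend on them. It should be corrected before analysis.

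**What to change.** Keep the pooled contrast as the primary test. For secondary outcome 1, and as a supporting overall analysis, code treatment as tonic, DTM and FAST on Stim-1 and Stim-2, with period effects and allowance for within-patient correlation. Report the DTM-tonic and FAST-tonic differences with 95% confidence intervals. Word the conclusion for the pooled class unless a pattern's own contrast supports a claim for it.

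No extra patients or assessments are needed. The costs to state openly are:

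- The contrasts are secondary and less precise than the pooled test. Power per pattern at 80% versus 50% is about 82% to 97% from Stim-1 and Stim-2, and about 62% in the Stim-1 fallback. A smaller true benefit will often not reach significance, so the intervals matter more than the p-values.
- Estimates by disease will be imprecise.
- The statement that multiplicity need not be considered must be limited to the pooled primary test.
- A pooled win may have to be reported without a claim for one of the two patterns.

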### Secondary outcomes

The following secondary outcomes will be analyzed at the end of the SCS trial: (1) the relationship between causative disease and improvement rates by each stimulation pattern and (2) comparison of the improvement rates between DTM and FAST stimulation patterns in all cases and by causative disease.

After SCS system implantation, the efficacy of SCS is defined as when the VAS value decreases by 33% or more compared to the VAS value before the implantation. Long-term effect is defined as continuing the efficacy of SCS for more than 12 months. The following secondary outcomes will be assessed for six times during 24 months’ follow-up periods after the implantation (Table 2): (3) changes in assessment items including the VAS, SF-MPQ-2, PCS, and QIDS-J preoperatively, and at 1, 3, 6, 12, 18, and 24 months after the implantation; (4) preoperative factors associated with the long-term effects; and (5) adverse events related to this study 3 months after the SCS system implantation. Data will be presented as mean and standard deviation for continuous variables (including VAS score, SF-MPQ-2 score, PCS score, and QIDS-J score).

#### VAS

The VAS is a basic self-reported measure for assessing pain intensity. It is a horizontal line of 100 mm, with 0 mm (the left endpoint) denoting no pain and 100 mm (the right endpoint) indicating excruciating pain [21]. The participants will be requested to choose the location on the line that best indicates their pain level.

#### SF-MPQ-2

The SF-MPQ-2 consisted of 22 items to provide increased responsiveness [22]. Each item is evaluated with an 11-point scale (0 representing no pain and 10 representing the worst pain imaginable). The SF-MPQ-2 is divided into 4 subscales, including 3 sensory descriptors and 1 affective descriptor, as follows: continuous pain descriptors (6 items), intermittent pain descriptors (6 items), predominantly neuropathic pain descriptors (6 items), and affective descriptors (4 items). The total pain dimension parameter is the sum of the sensory and the affective dimension of the pain (score range: 0 to 220). A high score indicates a high level of pain.

#### PCS

The PCS is used to measure pain-related catastrophic thoughts and consisted of 13 items [23]. Each item is scored on a 5-point Likert scale; evaluations (0 = not at all to 4 = always) are made. The scale assesses catastrophic thinking/feeling regarding 3 components: rumination, magnification, and helplessness. The total score range is from 0 to 52 points, and a higher score indicates a higher level of pain-related catastrophic thoughts.

#### QIDS-J

The QIDS-J consists of 16 questions and plays a role in the diagnostic criteria for major depressive disorder [24]. These questions are divided into nine categories. Four concerned sleeping disorders, four appetite and body weight, two psychological disorders, and the remaining nine other topics. The total score range is from 0 to 48 points, and a higher score indicates a higher level of depressive disorder.

### Sample size

The study’s sample size is based on the expected difference of the percentage of patients achieving pain improvement between the new and conventional tonic stimulation patterns.

We assumed that the percentages of pain improvement will be 80% for the new stimulation patterns (DTM or FAST) [15, 17] and 50% for the conventional tonic stimulation pattern [25–28] by reviewing the literature. The required sample size was calculated to be 78 cases with a significance level of 0.05, a power of 80%, and 1:1 allocation. Each group (A, B, C, and D) will enroll 20 cases (40 conventional tonic stimulation and 40 new stimulation patterns in Stim-1). Thus, it is possible to secure a power of 0.8 even with the analysis of Stim-1 alone. In addition, considering the insufficient sample size caused by patient detachment during the research process, it is necessary to expand the target number of cases is 23 in each group, resulting in a total sample size of 92 patients in all groups. Assuming, based on past performance, that there are 2–4 cases enrolled in the SCS trial per month, 24–48 patients are expected to be enrolled annually. Therefore, the target number is expected to be reached in 2 to 4 years.

### Concealment mechanism

The results of the allocation will be shown via the interactive web response system.

### Assignment of interventions: blinding

#### Who will be blinded

The randomization is single-blinded, i.e., participants do not know which group they are allocated to. Blinding of the researchers and data analysts is not possible because each stimulation pattern is not able to be completely concealed.

#### Procedure for unblinding if needed

Unblinding will not be needed because this study is single-blind.

#### Plans to promote participant retention and complete follow-up

Medical interviews and adjustments of the SCS parameters will be booked for all patients.

#### Confidentiality

The form used to code patients will be stored in a locked cabinet with logged access only available to the researchers and administrators responsible for the study.

#### Plans for collection, laboratory evaluation, and storage of biological specimens for genetic or molecular analysis in this trial/future use

Not applicable. No biological specimens will be involved in this study.

### Statistical analysis

The primary analysis will be performed after the completion of the SCS trial of the final registered participant. An analysis of the 12-month follow-up period data will be performed at the completion of the 12-month follow-up after the implantation of the final registered participant. Analyses of the 18- and 24-month follow-up period data will be performed at the completion of 24-month follow-up from the implantation of the final registered participant.

The primary outcome analysis will be as follows. Pain improvement will be compared between each stimulation using logistic regression analysis with explanatory variables of stimulation timing (Stim-1, Stim-2), treatment group (new stimulation patterns, conventional tonic stimulation), pre-VAS score for each stimulation pattern, and interaction between stimulation timing and treatment group. The carryover effect will be examined by testing the interaction terms with a significance level of 10%. If there is no carry-over effect, treatment groups will be compared with a significance level of 5%. If a carryover effect is observed, analysis will be performed with data from Stim-1 only.

The secondary outcome will be analyzed as follows:Similar analyses of the primary outcome analysis will be performed for each causative disease.Comparison of DTM and FAST stimulation patterns for pain improvement in Stim-3. Pain improvements will be compared between DTM and FAST stimulations using logistic regression analysis adjusted for the treatment group (DTM stimulation, FAST stimulation) and pre-VAS value. Similar analyses will be performed by causative disease.Adjusted mean values and 95% confidence intervals of changes in assessment items including the VAS, SF-MPQ-2, PCS, and QIDS-J before the SCS system implantation, and at 1, 3, 6, 12, 18, and 24 months after SCS system implantation at each time point will be calculated using a linear mixed model with the interaction between treatment group and time point as a fixed effect. Analysis will be performed using a linear mixed model with the change rate and change amount of each indicator as outcome variables. The rate and amount of changes in each index at each evaluation time point will be compared between groups using fixed effects such as pretreatment value of each index, treatment group, evaluation time point, and interaction between the treatment group and evaluation time point. The 12-month analysis will be performed at preoperative, 1, 3, 6, and 12 months, and the 24-month analysis will be performed at 18 months and the final follow-up (24 months).In participants with no missing VAS values preoperatively to 12 months after implantation, analyses of the prognostic factors related to the long-term effect of continuing 33% reduction in the pain VAS over 12 months will be performed using logistic analysis with the following explanatory variables: treatment group, pre-implantation VAS value, sex, age, causative disease, site of pain, degree of paralysis, degree of sensory disturbance, and disease duration.

A comparison between the new and conventional stimulation patterns will be performed with Stim-1and Stim-2. A comparison between DTM and FAST, which is the new stimulation pattern, will be performed with Stim-3. Therefore, this study is designed to compare the VAS improvement rates in different stimulation patterns, so it is not necessary to consider multiplicity.

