## Methods/design

### Study design

This is a single-center, open-label, crossover, randomized, superiority clinical trial.

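### The primary logistic regression on Stim-1 and Stim-2 does not account for two outcomes per participant, so the treatment test is too conservative and the carryover test declares carryover too often

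*Protocol article*

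**What the plan says.** The Study design section states: "This is a single-center, open-label, crossover, randomized, superiority clinical trial". Table 1 gives every participant tonic stimulation once and one new pattern once across Stim-1 and Stim-2. Groups 1 and 3 start with tonic; groups 2 and 4 start with a new pattern. The Statistical analysis section confirms that both periods feed the primary comparison: "A comparison between the new and conventional stimulation patterns will be performed with Stim-1and Stim-2".

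The outcome in each period is binary, "defined as effective when the VAS value decreases by 33% or more compared to the VAS value before the start of each stimulation pattern" (Primary outcome). The primary model is described as follows: "Pain improvement will be compared between each stimulation using logistic regression analysis with explanatory variables of stimulation timing (Stim-1, Stim-2), treatment group", then "pre-VAS score for each stimulation pattern, and interaction between stimulation timing and treatment group".

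The interaction then decides which data are used. "The carryover effect will be examined by testing the interaction terms with a significance level of 10" percent. "If there is no carry-over effect, treatment groups will be compared with a significance level of 5" percent. "If a carryover effect is observed, analysis will be performed with data from Stim-1 only".

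For the repeated measures after implantation, the same section names a linear mixed model. For the primary outcome it names only logistic regression.

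**The concern.** Two outcomes from one participant are likely to be correlated. Someone whose pain responds to stimulation, or whose leads are well placed, tends to do better under both patterns. The rule that a missing outcome counts as no improvement adds to this, because a participant who leaves before any assessment is a failure in both periods.

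An ordinary logistic regression takes the two rows as independent, which distorts the two key tests in opposite directions. The treatment effect is a within-participant contrast, so its standard error comes out too large. The interaction compares participants' two-period totals between orders, so its standard error comes out too small.

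At stake are the calibration of the primary test and any interval reported with it, power if the true effect is smaller than planned, and how often the gate sets aside half the data. The analyses by causative disease repeat the same model and inherit the problem.

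**Working it through.** **The plan's own figure.** Sample size inputs: 80% versus 50%, significance level 0.05, power 80%, 1:1. Taken as two-sided with pooled variance, n per arm = [1.96·√(2·0.65·0.35) + 0.842·√(0.25 + 0.16)]² / 0.30² = (1.322 + 0.539)² / 0.09 ≈ 38.5, so 39 per arm and 78 in total. This matches. It treats Stim-1 as a parallel comparison with one outcome per participant, so it does not depend on the point at issue. Power at 40 versus 40 is 81.6%.

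**Which contrast is which.** Let A be tonic first and B new first, with mean response A1, A2, B1, B2 (on the model's scale).
- Treatment: (B1 − A1) + (A2 − B2) = (A2 − A1) + (B1 − B2), which is built from within-participant differences.
- Interaction: (B1 − A1) − (A2 − B2) = (B1 + B2) − (A1 + A2), which compares participant totals between orders.

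With common variance σ² and within-participant correlation r, a difference has variance 2σ²(1 − r) and a total 2σ²(1 + r). The ordinary model uses 2σ² for both. Actual test sizes are then approximately
- treatment, nominal 5%: 2·[1 − Φ(1.96/√(1 − r))]
- carryover, nominal 10%: 2·[1 − Φ(1.645/√(1 + r))]

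| r (assumed) | Treatment test | Carryover test |
|---|---|---|
| 0.2 | 2.8% | 13.3% |
| 0.33 | 1.7% | 15.4% |
| 0.5 | 0.6% | 17.9% |

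**Bound on r.** At 80% versus 50% the two binary outcomes cannot correlate above (0.5 − 0.8·0.5)/(0.5·0.4) = 0.1/0.2 = 0.5. The table therefore stops there.

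**Simulation.** 80 participants, 40 per order, 4,000 runs per setting, no true carryover. The listed terms were fitted with ordinary and with participant-clustered standard errors, and treatment was tested without the interaction. The correlation is set on an underlying normal scale; 0.3, 0.5 and 0.7 there correspond to about 0.20, 0.33 and 0.50 between the binary outcomes at equal 50% rates.

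| Underlying correlation | 0 | 0.3 | 0.5 | 0.7 |
|---|---|---|---|---|
| Treatment, 5%, ordinary | 4.8% | 3.2% | 1.4% | 0.8% |
| Treatment, 5%, clustered | 5.2% | 5.3% | 4.6% | 5.8% |
| Carryover, 10%, ordinary | 9.2% | 14.0% | 14.2% | 18.9% |
| Carryover, 10%, clustered | 9.4% | 10.9% | 9.5% | 10.3% |
| Carryover at 80% vs 50%, ordinary | 10.6% | 11.5% | 14.9% | 15.8% |

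At underlying correlation 0.5 the treatment standard error is 0.320 ordinary against 0.263 clustered (observed spread of the estimates 0.260). For the interaction it is 0.647 against 0.749 (observed 0.743). The ratios, 1.22 and 0.86, agree with 1/√(1 − 0.33) and 1/√(1 + 0.33).

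**Power.** At 80% versus 50% the treatment test has at least 98% power with either method. At 70% versus 50%, which is not a protocol figure, it has 76/78/80% ordinary against 82/88/95% clustered at underlying correlations 0.3/0.5/0.7, a loss of 6 to 15 points.

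**Whole two-stage procedure, no true effect.** Gate plus final test runs at about 4–6% with ordinary standard errors and about 7–9% with clustered ones, depending on correlation and simulation settings. With ordinary standard errors the conservative treatment test partly hides the inflation that the gate causes.

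**The case against.** The strongest reply is that the text never says that rows are treated as independent. It lists explanatory variables, and a cluster identifier or robust variance is not one; the mixed model is also described by its fixed terms alone. An unseen analysis plan could add a participant effect. This stands as a limit on certainty: independence is inferred. But the article goes as far as fixing the model type and its terms for a two-period crossover, and names a mixed model elsewhere. Read plainly, the stated model does not fit the stated design.

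It can also be said that the harm is modest. The treatment test errs on the safe side, the planned effect leaves power to spare, and the Stim-1 fallback has one row per participant and is what the trial was sized for. All of this stands, and it limits the severity.

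Two stronger readings do not hold. A reader might infer that ignoring the pairing inflates false claims of superiority; with positive correlation the two-period treatment test is conservative. A reader might also infer that the trial is too small or that 78 is wrong; that figure reproduces and rests on Stim-1 alone.

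**Conclusion.** The point holds, conditional on the model being fitted as written and on positive within-participant correlation. For a binary correlation of about 0.2 to 0.5, the treatment test runs at about 0.5–3% instead of 5%. False carryover runs at about 13–18% by formula (up to 19% in simulation) instead of 10% at equal response rates, and at about 11–16% at 80% versus 50%. The documents give no correlation. At zero both errors vanish; if it were negative, their directions would reverse. Adjusting for the pre-stimulation VAS removes only the part of the correlation that it explains.

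The consequences are a miscalibrated primary test, a gate that discards Stim-2 more often than stated, and lost power if the effect is smaller than planned. At the planned rates the treatment test's power is not in danger. This should be fixed, but it does not invalidate the trial.

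**What to change.** 1. Keep the listed terms, but fit the model as a GEE logistic regression clustered on participant with robust standard errors, or as a random-intercept logistic model. State which: the first gives a population-averaged odds ratio, the second a participant-specific one.
2. Take the primary treatment effect from the two-period model without the interaction term. With the interaction kept and Stim-1 as the reference period, the treatment coefficient is the Stim-1 effect only.
3. Do not add clustering and leave the gate in place, since overall type I error would then be about 7–9%. Make the clustered two-period analysis primary whatever the carryover test shows, and report the interaction and the Stim-1-only result as supportive. This relies on the 1-day stimulation-off period as washout, and the plan should say so.
4. Apply the same specification to the analyses by causative disease.

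The cost is a few sentences in the analysis section, passed through the amendment route that the article describes. It needs no new data, no change in sample size and no change in trial conduct. It should be settled before the primary analysis.
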